### Data Collection

Trial-specific data collection is limited to the minimum required to deliver trial objectives and will be collected at baseline (before randomization), daily, at discharge from PICU, and 30 days, 90 days, and 12 months following randomization (**Table 4**; and **Case Report Forms**, Supplementary Materials, http://links.lww.com/PCC/C509). The PRESSURE team will work closely with PICANet to make the best use of routinely collected PICU data, which includes baseline demographics, severity of illness scoring, and daily critical care interventions.

**TABLE 4. T4:** Patient Data Collection Schedule

	Baseline (At Point of Randomization)	During Critical Care Unit Stay	End of Critical Care Unit Stay	At Hospital Discharge	At 1 yr
Patient details	✓				
Clinical/baseline data	✓				
Mean arterial pressure/vasopressors data	✓	✓	✓		
Cointerventions data		✓	✓		
Safety monitoring data		✓	✓		
Discharge data				✓	
Pediatric Quality of Life Inventory questionnaire (31)					✓
Child Health Utility 9D Index (32)					✓
Health services/resource use					✓

## STATISTICAL METHODS

### Sample Size

Mortality at 30 days and IMV days were estimated for the usual care arm using observational data from 4126 eligible sequential admissions to the FEVER study (investigating temperature thresholds for antipyretic intervention in critically ill children) (26), representing 39% of all unplanned admissions to U.K. NHS units reporting to PICANet in 2017 (4). Power estimates were based on 10,000 simulated trial datasets, using distributions of mortality and duration of IMV support (log-normal distribution with mean 7.8 and sd of 9.5 d). To achieve 90% power to detect a clinically meaningful reduction in mortality of 2% from 13% to 11% and the mean duration of IMV support of 18 hours from 7.8 to 7.1 days and allowing for 10% withdrawal/refusal of deferred consent requires a total sample size of 1900 patients. The same sample size will retain at least 80% power with either a mean reduction of 15 hours IMV support and a 2% reduction in mortality, or a mean reduction of 18 hours IMV support and a 1% reduction in mortality.

### Clinical Effectiveness Analysis

All analyses will be logged in a statistical analysis plan, a priori, before the investigators are unblinded to any study outcomes. All analyses will follow the intention-to-treat principle. Baseline patient characteristics will be compared between the two groups to observe balance and the success of randomization. These comparisons will not be subjected to statistical testing.

The analysis of the primary, composite, outcome will use rank-based methods, with death during the first 30 days following randomization ranked as the worst outcome and surviving patients ranked according to their duration of IMV support (30). The ranked outcomes will be compared between groups using a two-sample rank-sum (Wilcoxon-Mann-Whitney) test. The primary effect estimate will be the probabilistic index (the probability that the intervention is superior to the control for either mortality and/or duration of IMV support), which will be presented with a 95% CI. Duration of IMV support in surviving patients and mortality at 30 days will also be presented separately by arm with effect sizes and 95% CIs, in line with published guidelines for the use of composite primary endpoints (31).

Secondary analyses of mortality will be performed by Fisher exact test and adjusted logistic regression. Duration of survival to 12 months will be plotted as Kaplan-Meier survival curves, compared unadjusted with the log-rank test, and adjusted using Cox regression models. Time to first liberation from IMV will be analyzed by the log-rank test, with patients who die during IMV support treated as censored. Analyses of the length of PICU and hospital stay will be performed by rank-sum tests, stratified by survival status. Functional status will be assessed using the Pediatric Overall Performance Category and Pediatric Cerebral Performance Category scales (32). Healthcare-related quality of life (HRQoL) will be assessed using Pediatric Quality of Life Inventory (33) and Child Health Utility 9D Index (34) questionnaires at 12 months. Analyses of these data will be performed by *t*-tests and adjusted linear regression.

The primary endpoint and some secondary endpoints, will be reported in a limited number of prespecified clinically relevant subgroups, which will include patients classified by age. Results will be interpreted taking account of accepted criteria for credible subgroup effects (35, 36). A single interim analysis will be undertaken after recruitment and follow-up to 30 days of 50% of patients using a Peto-Haybittle stopping rule (*p* < 0.001) for termination due to either benefit or harm.

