### Screening and Randomization

Potentially eligible patients admitted (or accepted for admission) to participating PICU will be screened against the inclusion/exclusion criteria by the local clinical or transport team (**Table 1**). Patients will be randomized in a ratio 1:1 to either usual care or a permissive MAP target (fifth centile for age), stratified by site and age group (< 1, 1–3, ≥ 3 yr), to ensure balanced strata sizes. Randomization must occur within 6 hours of all the eligibility criteria being satisfied (Table 1). Randomization will be done by an automated randomization server accessible both by telephone and via web browser. The randomization sequence is computer-generated and will use variable block sizes to strengthen allocation concealment.

**TABLE 1. T1:** Eligibility Criteria

Inclusion criteria
• Age > 37 wk corrected gestational age and < 16 yr
• Enrolled within 6 hr of first meeting all the following criteria;
◦ Accepted for or admitted to a participating PICU
◦ Face-to-face contact with PICU staff or transport team
◦ On invasive mechanical ventilation
◦ Receiving a continuous infusion of vasoactive drug for hypotension
◦ Vasoactive drug expected to continue for at least 6 hours or more^a^
Exclusion criteria
• Admitted postcardiac surgery
• Known cardiomyopathy^b^
• Neonates with suspected or proven duct-dependent circulation
• Acute brain injury^c^
• Currently being treated for pulmonary hypertension
• Admitted with malignant hypertension
• Death perceived as imminent
• Previously recruited to Protocolised Evaluation of Permissive Blood Pressure Targets Versus Usual Care trial

a “Vasoactive drug expected to continue for at least 6 hours or more” is at the discretion of the clinical team.

b “Known cardiomyopathy” refers to conditions known at time of randomization.

c “Acute brain injury” refers to traumatic brain injury or any acute or evolving neurologic condition requiring a neurointensive care strategy. In general, patients post cardiac arrest would not be eligible for randomization due to the high likelihood of acute brain injury. If the clinical team can rule out this contraindication (e.g., brief in-hospital cardiac arrest, when acute brain injury is not suspected) the patient would be eligible.

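### The primary rank-sum test and probabilistic index ignore the site and age strata used in randomisation, so they are conservative if those factors are prognostic

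*Protocol article*

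**What the plan says.** Under Screening and Randomization, allocation is 1:1 in variable blocks, "stratified by site and age group (< 1, 1–3, ≥ 3 yr), to ensure balanced strata sizes". Design and Setting gives 18 PICUs, so there are up to 18 × 3 = 54 strata.

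Under Clinical Effectiveness Analysis, the composite is ranked "with death during the first 30 days following randomization ranked as the worst outcome and surviving patients ranked according to their duration of IMV support". The test is then fixed: "The ranked outcomes will be compared between groups using a two-sample rank-sum (Wilcoxon-Mann-Whitney) test". "The primary effect estimate will be the probabilistic index", "which will be presented with a 95% CI". Site and age group appear in neither the test nor the estimate.

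Adjustment is named for some secondary outcomes, for example: "Secondary analyses of mortality will be performed by Fisher exact test and adjusted logistic regression". Adjusted Cox models are named for survival and adjusted linear regression for quality of life. Age returns only as a subgroup factor.

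**The concern.** Blocked randomisation within strata forces the arms to be nearly balanced on site and age group. Differences in outcome between strata therefore contribute almost nothing to the chance difference between arms. The null variance of the two-sample rank-sum test takes no account of this and counts between-stratum variation as noise. Where strata are prognostic, the standard error is too large for the design used: the test rejects less often than 5% under the null, and the interval for the probabilistic index is wider than it need be.

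At stake are the primary p-value, the width of the primary interval and some power. Site and age group are known for every patient at randomisation, so using them needs no new data.

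**Working it through.** **Inputs from the protocol article.** Sample Size: mortality 13% vs 11%; log-normal ventilation days with mean 7.8 and SD 9.5; a reduction of 18 hours (7.05 days exactly, printed as 7.1); 1900 randomised with 10% withdrawal, so 1900 × 0.9 = 1710 analysed, 855 per arm. Two-sided 5% is assumed from the 95% CI.

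**Step 1: reproduce the stated power of the unstratified test.** Further assumptions: SD 9.5 in both arms, duration capped at 30 days, death ranked worst.
- Null SE of the index ≈ √[1711 / (12 × 855²)] = 0.0140, or 0.01395 after correction for ties.
- At 7.05 days the index is 0.5462. Power = Φ(0.0462/0.01395 − 1.96) = 91.2%.
- At 7.1 days the index is 0.5438, and power is 88.0%.
- Fallback scenarios: 15 hours with 2% mortality gives 81.9%; 18 hours with 1% gives 83.3%.

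The stated 90%, and at least 80% in the fallbacks, therefore hold for the plain test.

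**Step 2: analytic effect of ignoring the strata.** Let R² be the share of rank variance explained by the strata. The documents give no value, so 5% to 15% is an assumed range. Under stratified blocking, the plain z statistic has variance of about 1 − R². With 90% nominal power, the mean of z is 1.96 + 1.2815 = 3.2415.
- True size = 2[1 − Φ(1.96/√(1 − R²))]
- Power, plain test = Φ(1.2815/√(1 − R²))
- Power, stratified analysis = Φ(3.2415/√(1 − R²) − 1.96)
- Patient equivalent = 1710 × {[1 + 1.96(1 − √(1 − R²))/3.2415]² − 1}, the extra patients the plain test would need to match

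| R² | True size | Plain | Stratified | Gain (points) | Patients |
|---|---|---|---|---|---|
| 5% | 4.4% | 90.57% | 91.40% | 0.8 | 53 |
| 10% | 3.9% | 91.16% | 92.74% | 1.6 | 108 |
| 15% | 3.4% | 91.77% | 94.01% | 2.2 | 165 |

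**Step 3: simulation.** 1710 patients in 54 unequal strata, permuted blocks of 4 or 6 (assumed, as sizes are not given), a 7.05-day mean under the alternative, and 8000 trials per setting. The share here is of latent outcome variance between strata, which is not the same scale as R² above.

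| Share | Type I, plain / van Elteren | SD of plain null z | Power, plain / van Elteren | Change (points) |
|---|---|---|---|---|
| 0% | 0.049 / 0.050 | 0.991 | 90.8% / 90.1% | −0.7 |
| 5% | 0.045 / 0.049 | 0.975 | 91.3% / 91.8% | +0.4 |
| 10% | 0.034 / 0.044 | 0.932 | 91.7% / 93.1% | +1.4 |
| 20% | 0.029 / 0.052 | 0.885 | 93.7% / 96.1% | +2.4 |

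Monte Carlo error is about 0.25 points on type I error and 0.3 on power. The excess width of the plain interval is 1/SD − 1: 2.6%, 7.3% and 13.0% at shares of 5%, 10% and 20%.

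**Step 4: sensitivity to the form of the effect.** If the coefficient of variation, not the SD, is held constant, base power is only about 61%, and stratifying changes it by about −1 to +9 points (3000 trials per setting). That case does not reproduce the plan's 90%, so it is not used for the conclusion.

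**The case against.** The strongest reply is that nothing is invalid. The comparison is randomised, the test errs on the safe side, and the stated power is met. That stands. A reader might infer that ignoring the strata inflates type I error or leaves the trial underpowered. Steps 1 to 3 show neither.

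The loss is also conditional. With no stratum effect the plain test is slightly better (90.8% vs 90.1%), and the documents give no prognostic strength for site or age. That stands too.

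A reader might hold the planned test at 90% and credit the stratified analysis with gains of 1.4, 2.7 and 4.0 points, or about 90, 190 and 300 patients. This overstates the benefit. The variance reduction that makes the plain test conservative also raises its own power, to 90.6%, 91.2% and 91.8%. The like-for-like gain is a little over half as large.

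The contrast with secondary outcomes is weaker than it looks. The plan mostly pairs an unadjusted with an adjusted analysis. Time to liberation has only a log-rank test, and lengths of stay are stratified by survival status, not by site or age. An adjusted analysis of the primary outcome may also be in the statistical analysis plan, which is not shown. But the article positively names the unstratified test as primary, so the point concerns a stated rule and not an omitted detail.

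Finally, stratifying changes the target. The index as written compares the arms overall, whereas a stratified index compares patients within strata. This is a real cost and is carried into the fix.

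**Conclusion.** The point holds in conditional form. Design and primary analysis do not match. If site or age is prognostic, the primary p-value and interval are conservative: size is about 4.4% to 3.4% for an assumed 5% to 15% of rank variance explained. Accounting for the strata adds about 0.8 to 2.2 points of power by formula, and about 0.5 to 2.5 points by simulation for latent shares of 5% to 20%.

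These figures rest on assumed prognostic strength, two-sided 5% testing, and SD 9.5 in both arms. The documents do not support calling the trial underpowered or the test anti-conservative. This is a worthwhile, inexpensive improvement to the primary analysis and no more.

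**What to change.** Before unblinding, amend the primary analysis so that the test and the probabilistic index, with its interval, account for the randomisation strata. Either:
- a van Elteren test over the strata with a matching stratified index; or
- a probabilistic-index or proportional-odds model with age group and site, with site as a random effect to avoid sparse cells.

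Keep the plain rank-sum test as a sensitivity analysis. Use the age strata as programmed in the randomisation server, because the printed bands overlap at age 3 (a separate wording point).

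Add a severity score only if it is measured before randomisation. Data Collection describes the PICANet data as data "which includes baseline demographics, severity of illness scoring, and daily critical care interventions", without saying that the score precedes randomisation, and transport teams may screen patients accepted for admission before they arrive.

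**Cost.** A change of wording and no new data. If strata carry no information and all 54 cells are used, about 1 to 2 points of power are lost. The main simulation gives 0.7. A smaller run of 1000 trials per setting gives 1.9 (82.9% to 81.0%), but its baseline does not match the plan's 90%, so it is only a rough upper figure. The stratified index must be described as a within-stratum comparison; the model-based options rest on a model assumption.

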**SETTING::**

Eighteen PICUs across the United Kingdom.

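### Randomisation is blocked within site and age group, but the primary rank-sum test ignores both, so its p-value is conservative to whatever extent site or age predicts the outcome

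*Protocol article*

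**What the plan says.** Under Screening and Randomization, allocation is 1:1, "stratified by site and age group (< 1, 1–3, ≥ 3 yr), to ensure balanced strata sizes". The same paragraph adds: "The randomization sequence is computer-generated and will use variable block sizes to strengthen allocation concealment". The abstract gives the setting as "Eighteen PICUs across the United Kingdom", so there are 18 × 3 = 54 strata.

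Under Clinical Effectiveness Analysis, the primary comparison is: "The ranked outcomes will be compared between groups using a two-sample rank-sum (Wilcoxon-Mann-Whitney) test". On the estimate it says: "The primary effect estimate will be the probabilistic index", to be given with a 95% CI. No stratification or adjustment is attached to the test or to the index, and no interval method is named.

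The same section does specify stratification or adjustment for other outcomes. For length of stay: "Analyses of the length of PICU and hospital stay will be performed by rank-sum tests, stratified by survival status". For mortality: "Secondary analyses of mortality will be performed by Fisher exact test and adjusted logistic regression". Duration of survival has a log-rank test and adjusted Cox models, and quality of life has adjusted linear regression. Time to first liberation from ventilation has a log-rank test only.

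**The concern.** Blocking within strata keeps the arms close to balanced on site and age, which removes most between-site and between-age variation from the treatment contrast. The ordinary rank-sum variance is derived for unrestricted allocation and still contains that variation. If the strata are prognostic, the reported standard error exceeds the true sampling error, so the p-value is too large and any interval built on it too wide. At stake is precision that the design has already bought through its randomisation and that the primary analysis does not use.

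This is more than detail left to an analysis plan. The article names the primary test, and names it without strata, in a section that writes strata or adjustment elsewhere when it intends them.

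A smaller point belongs with it. As printed, the age strata 1–3 and ≥ 3 both contain a 3-year-old. Table 2, in completed years, has bands ≥ 1–3 and 4–9. The strata have to be unambiguous before they can enter an analysis.

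**Working it through.** **Inputs from the article (Sample Size).** Total 1900 with 10% withdrawal or refusal, so 1900 × 0.9 = 1710 analysed, 855 per arm. Mortality 13% versus 11%. Control ventilation time: "log-normal distribution with mean 7.8 and sd of 9.5 d". Reduction of 18 h = 0.75 d, so 7.8 − 0.75 = 7.05 d (printed as 7.1). Power 90%.

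**Assumptions.** Two-sided alpha of 0.05 (not stated there, but consistent with the 95% CI). Block sizes 4 and 6 (not given). R², the share of rank variance explained by site and age, is not given and is shown as a range.

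**1. The stated power.** The plain rank-sum test was simulated (2000 trials per setting) with deaths ranked worst, time capped at 30 days and SD 9.5 d in both arms. Power was 91% with 7.05 d (88.5% with the rounded 7.1 d), 81% for 15 h and 2%, and 83% for 18 h and 1%. The article's 90% and at least 80% are therefore reproduced with the unstratified test.

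**2. Standard error and alpha.** With stratified blocking the true standard error is about √(1 − R²) times the rank-sum one, so the planned one is too large by the factor k = 1/√(1 − R²). True alpha is 2[1 − Φ(1.96k)].

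| R² | k | 1.96k | true alpha |
|---|---|---|---|
| 0 | 1.000 | 1.960 | 5.0% |
| 2% | 1.010 | 1.980 | 4.8% |
| 4% | 1.021 | 2.000 | 4.5% |
| 9% | 1.048 | 2.055 | 4.0% |

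A simulation of 1710 children in 18 unequal sites and 3 age groups (4000 null trials per setting) gave 4.9%, 4.6% and 4.1% at R² of 2%, 4% and 9%. Ranks regressed on arm, site and age gave 5.0–5.2%. The null SD of the plain z was 0.990, 0.979 and 0.954, against √(1 − R²) = 0.990, 0.980 and 0.954. The Monte Carlo error of each alpha is about √(0.05 × 0.95/4000) = 0.34 points. The 4.9% and 4.6% therefore cannot individually be told from 5%; the case at small R² rests on the formula and on the SDs of z.

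**3. Power.** For 90% nominal power the standardised effect is δ = 1.960 + 1.282 = 3.242. Plain test: Φ[(δ − 1.960)k]. Adjusted test: Φ[δk − 1.960].

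| R² | plain | adjusted | simulated plain → adjusted |
|---|---|---|---|
| 2% | 90.2% | 90.6% | 90.5% → 90.9% |
| 4% | 90.5% | 91.1% | 90.5% → 91.2% |
| 9% | 91.0% | 92.5% | 90.8% → 92.4% |

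With no stratum effect the simulation gave 90.2% and 90.1%, a difference within simulation error. The plain test does not fall below its nominal power in any row.

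**4. Interval width.** The null standard error of the index from the plain formula is 0.01395, so the 95% half-width is 1.96 × 0.01395 = 0.0273. Dividing by k gives 0.0271, 0.0268 and 0.0261 at R² of 2%, 4% and 9%. This applies only if the CI is taken from the rank-sum variance.

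**5. The estimate.** In a regression of overall ranks on arm alone, the arm coefficient equals N times (index − 0.5), apart from sign. Adding site and age left the mean estimate at 0.545 for both methods; single trials differed by up to 0.003.

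**6. Form of stratification.** A van Elteren test over all 54 cells (1710/54 ≈ 32 children each on average) also restores alpha: 5.0% against 4.3% for the plain test at a rank R² of about 6%. With uninformative strata it lost about one point of power (88.4% versus 89.7%). The additive rank model did not.

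**The case against.** The strongest reply is that the effect is small, harmless in direction and of unknown size. That largely stands. No R² is given, every figure above is conditional, and at 2% or less the effect is negligible; one simulation at about 2% showed plain-test alpha of 5.1%, that is, no visible conservatism. The article's power calculation also agrees with the test it names.

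It can also be said that the interval method and covariates may be set in the analysis plan, which is not shown. For the interval this stands, and the CI part of the point is conditional for that reason. For the primary test it does not, because the article fixes that test.

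Two stronger readings are tempting.

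- A reader might infer that the primary analysis is invalid or the trial underpowered. The documents do not support this: the estimate is unbiased, the error is on the conservative side, and the 90% is reproduced without any adjustment.
- A reader might infer that the mortality and survival analyses also ignore the design. Adjusted logistic and Cox models are already named for them, and not listing their covariates is normal in an article. The known conservatism of Fisher's test comes mainly from discreteness and says nothing about ignored strata.

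The age overlap does not affect an unstratified test and adds no weight to the main point. It matters once age group enters an analysis.

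**Conclusion.** The point holds as a conditional efficiency point: the direction is firm and the size is not. It rests on stratified blocks being used as described, on two-sided alpha of 0.05, and on an assumed R². From 2% to 9%, the standard error is 1% to 5% too large, true alpha is 4.8% to 4.0%, and about 0.4 to 1.6 points of power are unused. At R² = 0 nothing is lost. The CI of the index shares the excess width only if it is derived from the rank-sum test. The change is worth making because it costs almost nothing; the planned analysis would remain valid without it.

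**What to change.** - Keep the rank composite and the probabilistic index. Take the primary p-value and 95% CI from a rank analysis that includes the randomisation factors, for example overall ranks regressed on arm, site and age group. The sign-reversed arm coefficient divided by N is the index minus 0.5, essentially unchanged from the plain estimate.
- Prefer this additive form to a test stratified over all 54 cells. If a fully stratified test is chosen, state a rule for sparse cells.
- Report the plain rank-sum test as a sensitivity analysis, and name the interval method for the index.
- Use the age groups exactly as coded in the randomisation server and print them without overlap.
- Among the secondary outcomes, stratify or adjust the log-rank test for time to first liberation from ventilation, which has no adjusted counterpart.

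The cost is a few sentences of plan wording and a few lines of code, with no new data, patients or visits. The change should be written in before the investigators are unblinded to outcomes. The only downside is that there is no gain if site and age prove not to be prognostic.

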## OUTCOME MEASURES

The primary clinical effectiveness outcome is a composite of mortality and duration of IMV, defined by the U.K. Paediatric Critical Care Minimum Dataset (28), from randomization to day 30. This will include any periods of reintubation. This outcome measure was chosen based on previous qualitative work which highlighted the child “looking and feeling more like themselves” and “time on machines” as the most important outcomes for parents (29). As intensive care interventions for cardiovascular support will be different between the intervention and control arms, the focus of the primary outcome measure is on respiratory support. Some other forms of organ support (e.g., renal replacement therapy) will be assessed as a secondary outcome measure. A full list of trial outcome measures can be found in **Table 3**. Due to the nature of the trial, it will not be possible to blind the outcome assessments.

**TABLE 3. T3:** Trial Outcome Measures

Primary outcome—clinical effectiveness
• Composite of mortality and duration of invasive mechanical ventilation from randomization to day 30
Primary outcome—cost-effectiveness:
• Incremental net monetary benefit, evaluated at the U.K. National Instiute for Clinical Excellence recommended threshold of £20,000 per quality-adjusted life year at 12 mo
Secondary outcomes
• Mortality at PICU discharge, 30 d, 90 d, and 12 mo
• Duration of survival to 12 mo
• Time to first liberation from invasive ventilation
• Functional status change between PICU admission and PICU discharge, measured by the Pediatric Overall Performance Category and Pediatric Cerebral Performance Category scales (30)
• Receipt of renal replacement therapy at 30 d
• Length of PICU and hospital stay
• Health-related quality of life at 1 yr, measured by the child self- or parent-proxy reported Pediatric Quality of Life Inventory 4.0 (31) with age-appropriate versions covering the wide range included in the trial (1 mo–16 yr) and the Child Health Utility 9D Index (32)
• Incremental costs at 30 d

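### The log-rank test for time to first liberation censors deaths on the ventilator, so it compares only the cause-specific liberation hazard, not how many children are liberated or how soon

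*Protocol article*

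**What the plan says.** Table 3 of the protocol article (Outcome Measures) lists "Time to first liberation from invasive ventilation" as a secondary outcome. Clinical Effectiveness Analysis then fixes both the test and the handling of death: "Time to first liberation from IMV will be analyzed by the log-rank test, with patients who die during IMV support treated as censored". It names no competing-risk method for this outcome. Because the rule is written out, this is not a detail left to an unseen analysis plan.

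The same section treats death differently in other places. The primary composite is ranked "with death during the first 30 days following randomization ranked as the worst outcome and surviving patients ranked according to their duration of IMV support". It adds: "Duration of IMV support in surviving patients and mortality at 30 days will also be presented separately by arm with effect sizes and 95% CIs". The rank-sum tests for PICU and hospital stay are stratified by whether the child survived.

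**The concern.** Censoring suits a child whose liberation time exists but was not seen. A child who dies while ventilated has no such time. Censoring at death lets the children still ventilated stand in for that child, as if liberation were still to come at their rate.

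What remains is a comparison of the rate of liberation among children still alive and ventilated. A reader of an outcome called time to first liberation will probably take the result as an answer to whether children come off the ventilator sooner, or more often, on the permissive target. The two questions separate when the arms differ in deaths on the ventilator. The result could then be reported as no difference when fewer children were liberated. If the extra deaths removed slow-to-liberate children, it could be reported as faster liberation in the arm with more deaths. The loss works in both directions: a survival benefit that leaves the liberation rate unchanged is hidden too.

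**Working it through.** **Inputs from the documents (Sample Size).** Total 1900 with 10% loss: 1900 × 0.90 = 1710, or 855 per arm at 1:1. Thirty-day mortality is 13% under usual care and 11% at the target effect. Ventilation time is given as "log-normal distribution with mean 7.8 and sd of 9.5 d". The plan gives no figure for the liberation outcome. Its 90% power for the primary test does reproduce: 0.91 by simulation at 855 per arm, with an 18 h reduction, SD 9.5 d in both arms and an assumed two-sided 5% level. So 855 is a sound analysed size.

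**Assumed.** All hazards below, because the documents give no joint distribution of death and ventilation time.

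**Formulas.** With liberation hazard λ and death hazard δ per day:
- liberated by day t: λ/(λ+δ) × [1 − exp(−(λ+δ)t)]
- died on the ventilator by day t: δ/(λ+δ) × [1 − exp(−(λ+δ)t)]
- liberation curve implied by censoring deaths: 1 − exp(−λt), which does not contain δ.

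**Setting A: excess deaths, liberation hazard unchanged (λ = 0.15).**
- δ = 0.0225: liberated by day 30 = 0.15/0.1725 × (1 − e^−5.175) = 86.5%; died 13.0%.
- δ = 0.045: 0.15/0.195 × (1 − e^−5.85) = 76.7%; died 23.0%.
- δ = 0.027: 0.15/0.177 × (1 − e^−5.31) = 84.3%; died 15.2%.
- Curve with deaths censored: 1 − e^−4.5 = 98.9% in all three cases.

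Simulated log-rank tests, 855 per arm:
- 13% vs 23%: planned test significantly slower in about 3% of trials (chance); with deaths held as not liberated to day 30, 96%.
- 13% vs 15%: about 2% against about 15% (runs gave 14% to 15%; a further check of 3,000 trials gave 12.6%).

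An intermediate case with λ = 1/7.8 and mortality 13% vs 17% has 85.8% vs 82.0% liberated. The planned hazard ratio is 1.00, slower in 2.6% of trials; with deaths held it is 0.93, slower in 30%. In the direction the trial hopes for, 13% vs 11%, the planned test shows faster liberation in 2.3% and the held analysis in 12%.

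**Setting B: deaths confined to a slow-to-liberate 26% of children (λ = 0.04; λ = 0.20 in the rest).**
- Death hazard 0.05 in the slow group: died 0.26 × 0.05/0.09 × (1 − e^−2.7) = 13.5%; liberated 0.74 × (1 − e^−6) + 0.26 × 0.04/0.09 × (1 − e^−2.7) = 84.6%.
- Death hazard 0.10: died 0.26 × 0.10/0.14 × (1 − e^−4.2) = 18.3%; liberated 81.1%.
- Death hazard 0.065: died 0.26 × 0.065/0.105 × (1 − e^−3.15) = 15.4%; liberated 83.3%.

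Simulated:
- 13.5% vs 18.3%: the planned test declares the higher-mortality arm significantly **faster** in about 30% of trials (27.5% to 31% over runs; nominal 2.5%). With deaths held, it is faster in 0.2% and slower in about 20%.
- 13.5% vs 15.4%: planned test falsely faster in about 7%.

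**Sensitivity.** When death times were spread over the ventilation period, the planned hazard ratio stayed at 0.96 to 1.00. The faster appearance depends on which children die and when.

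**The case against.** The strongest reply is that a log-rank test with deaths censored is a correct test of the cause-specific liberation hazard. In setting A those hazards are equal by construction, so rejecting at chance level is proper behaviour. This stands. A reader might infer that the plan contradicts itself because its primary outcome ranks death worst. It does not: a secondary outcome may ask a different question. The fault is that the question tested is narrower than the outcome's name suggests.

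A reader might also infer that the trial could overlook excess deaths. The documents do not support that. Death is ranked worst in the primary outcome, mortality is reported by arm at several times with its own tests, and the interim analysis has a stopping rule for harm. A simple two-sided 5% comparison of deaths flagged the harm in 100% of simulated trials at 13% vs 23% and in 76% at 13.5% vs 18.3%. One qualification: at a 2-point excess such a comparison is seldom significant. At 13.0% vs 15.2%, z = 0.022/√(2 × 0.141 × 0.859/855) = 1.31, so power is about Φ(1.31 − 1.96) = 26%. The mortality estimates and their intervals would still be in the report.

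Three further limits stand:
- The planned 11% to 13% is all-cause 30-day mortality. It is an upper bound for death before first liberation, not its expected frequency.
- Nothing in the documents shows that deaths concentrate in the children ventilated longest, so setting B is a possibility and not a prediction.
- The article plans Kaplan-Meier curves for survival only. The overstated curve in setting A matters only if a liberation curve is drawn with deaths censored.

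**Conclusion.** The point holds for one secondary outcome. The planned test does not compare the proportion of children liberated or how soon they are liberated, because it ignores death as a competing event.

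The size depends on assumed hazards. The larger figures (96% against 3%, and 30% falsely faster) need mortality differences of about 10 and 5 points. At about 2 points, the scale the trial is planned on, they shrink to about 15% against 2%, and about 7% falsely faster. That excess deaths are invisible follows whenever they leave the liberation hazard unchanged. That the worse arm looks faster needs the further assumption that those deaths fall on slow-to-liberate children. The primary conclusion and the mortality results do not depend on this analysis, and they would usually show the excess deaths. The change is worth making but does not threaten the trial's main result.

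**What to change.** Before any unblinding, replace the censoring rule in the analysis plan and protocol:
- Treat death before first liberation as a competing event.
- Report the cumulative incidence of liberation by arm, with Gray's test or a subdistribution hazard ratio. Holding deaths as not liberated to the end of the follow-up window is an acceptable alternative.
- Keep the cause-specific log-rank result only beside the cause-specific hazard of death on the ventilator, and describe it as a comparison of liberation rates among children still ventilated.

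The cost is wording and a few lines of code, with no new data. The small downside is that a subdistribution hazard ratio is less intuitive, so the cumulative incidence curves should lead. The change corrects what the outcome measures. It is not a sensitive detector of excess deaths (about 20% in setting B at 13.5% vs 18.3%), and the mortality analyses should keep that role.
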